### Description of the intervention

#### Intervention group

The women in the intervention group will have the usual antenatal care, this is, at least one group lesson with theoretical-practical content about breastfeeding, as a part of the antenatal education taught by their reference health centre’s midwife, trained for that purpose.

Subsequently, in the first ten days after birth, they will have a preliminary individual appointment with their midwife, where individual doubts will be answered and obstetrical-neonatal data, related to birth and this subsequent period, will be collected. Data referred to in the WHO’s BREASTfeeding Observation Form [24], in the General Self-Efficacy Scale [25], and in the Breastfeeding Self-Efficacy Scale [26] will be collected as well.

The women will participate in monthly face-to-face, two-hour group sessions, called Breastfeeding Support Groups, where the midwife will act as a leading figure and moderator. These sessions will have an educational component, using theoretical-practical demonstrations related to breastfeeding themes, based on the Baby-Friendly Hospital Initiative (BFHI) [27] recommendations**.** Besides, there will be a motivational element and a component based on the social or the mother-to-mother support established in the group. During these sessions, the women will be able to share their concerns, experiences, and doubts and, furthermore, they will help each other with their own knowledge about breastfeeding. Should they find any difficulties, the midwife will take part as an expert on the topic, and as a moderator when answers are given among mothers with successful breastfeeding experiences. Thus, they will be offered monthly face-to-face, professional-led, organized, and proactive support.

Apart from these monthly meetings, the participants will have the choice of interacting with each other, with other lactating women, and with the reference midwife, using Facebook and WhatsApp groups created for that purpose. This way, mother-to-mother support can be reinforced and the resolution of doubts on the subject through Information and Communication Technologies (ICTs) [28] can be assessed. They will also have the option of arranging an individual appointment with their reference midwife, as well as the usual postnatal care. All of this will be recorded.

A follow-up at the first two, four, and six months after birth will be performed; at these points, the main outcome variables will be collected (current way of feeding, dropout register, obstacles, ICTs use register, neonatal admission, return to work) and the same scales as in the first visit, previously mentioned, will be once again administered.

#### Control group

The women in the control group will receive the usual antenatal care according to the pregnancy, birth, and postpartum care protocol of the Department of Equality, Health and Social Policies of the Regional Government of Andalusia [29], regarding antenatal and postnatal care, as well as the women in the intervention group.

Besides, they will have the option of asking for individual on-demand appointments with their reference midwife at the health centre they belong to.

The first postpartum visit will take place before the first ten days and the follow-up will be performed after the first two, four, and six months after birth; at these points, the main outcome variables will be collected (current way of feeding, dropout register, obstacles, ICTs use register, neonatal admission, return to work) and the same scales as in the first visit, previously mentioned in the intervention group, will be once again administered [24–26].

Figure 1 details the flow of participants from recruitment until the last follow-up contact for control and intervention subjects.

**Fig. 1 Fig1:**
[figure not shown]
Flow diagram of the participants through the trial

#### Data collection

Once the woman is randomized to the control or intervention group and has signed the written consent, having been previously informed of the study objectives, the midwife will let her know about the follow-up she will need to perform throughout the study. The woman will have to choose whether she prefers to be followed up via the GALMA Project application (App), or by filling in online questionnaires via WhatsApp®.

The previously mentioned basal follow-up will be conducted and the participants will have to facilitate the information using the study App, which will have previously sent a reminder message to them. Those women who opt to fill in online questionnaires will receive a phone call the previous day from a member of the research team, who will send to them the link to the questionnaires. Data related to the monitoring, both electronic and via the App, will be coded and saved by the research team. Those data related to obstetrical results and those derived from a hospital stay will be drawn from the patient’s medical record, after the patient’s consent.

Incorrect or missing data will be checked by the members of the research team and the participants will be asked for their fulfilment. All data will be recorded in an electronic database with access only by the team members. Hard copies of the participants’ questionnaires will be kept in a safe and secure file which can be accessed only with previous authorization.

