#### Participants, recruitment, and study area

Eligible female participants will be recruited in randomized primary health centres (clusters) in Andalusia, Spain. Andalusia is an Autonomous Community divided into 8 provinces with a total of 8,414,240 inhabitants (available data in 2019) [20], with a birth rate of 8.48 for each 1000 inhabitants (2018) [21]. By July 1st, 2019, the number of females in a reproductive age in Andalusia was 1,924,680 [22]. This is a multicentric study based on the Andalusian provinces of Seville, Huelva, Cádiz, Granada, and Jaén. Participant recruitment will be conducted on the antenatal care clinic at the 35th–37th week of pregnancy. Midwives will explore the women’s intentions regarding breastfeeding and whether or not they meet the inclusion criteria described below; they will also explain to them the purpose of the study including its risks and benefits. The women will be invited to participate voluntarily.

The eligibility criteria will be revised in the first postpartum visit for the women who accept to participate in both the control and the experimental groups.

Midwives meeting the criteria described below will serve as trained recruiters:
At least 2 years of professional experience as a midwifeNot having the intention of abandoning the work centre during the project time periodAttendance to the project’s training meetingSignature of the research agreement

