#### Randomization and data management

Centres are randomized to either an intervention arm or normal care. After this randomization, women are allocated either to the intervention group or to the control group by simple random sampling at the 35th–37th week of pregnancy by the midwives at the primary health centres, who will confirm that these women have the intention to breastfeed and that they have indeed initiated it in the first 10 days postpartum. Once the centre randomization for the recruitment of women for the control and intervention groups is conducted, these will be once again randomized following a simple randomization strategy. The participants’ recruitment will begin in September 2020, and will end in March 2022. This will be carried out by those midwives responsible for each health centre, being advised by one of the project’s experts.

These experts will work independently of the accountable researchers for the recruitment of participants. They will allocate health centres using a random sequence made by the *Oxford Minimization and Randomization (OxMAR)* system [23]. The experts will randomly assign a non-transferrable identifier to the health centres, making a difference between the control group and the experimental group centres. Subsequently, each participant will have an identification code depending on their group. This way, we intend to avoid the bias between two women attending antenatal care at the same centre who may or may not join the breastfeeding support group linked thereto, depending on whether they are allocated to one group or the other.

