### Ethics and dissemination

This study has been elaborated in strict compliance with the ethical principles of the Declaration of Helsinki (1964), subsequently revised in Tokyo (1975), Venice (1983), Hong Kong (1989), Somerset West (1996), Edinburgh (2000), Washington (2002), Seoul (2008), and Fortaleza (2013), including the informed consent request for the women participating in it.

Participation in the project is voluntary, as well as the participation request. The study has been laid out according to Spanish regulation act No. 14/2007 of July 3rd, regarding biomedical research, complying with the protocol suitability requirements and with the procedure regarding the study objectives. In the same way, the study will be conducted according to the Declaration of Helsinki.

All patient-related data collected for this study will be treated according to the Spanish Organic Law on Protection of Personal Data (Spanish Organic Law 15/1999) of December 13th and to European Regulation (EU) 2016/679 of the European Parliament and Council of April 27th, 2016, as well as to the established confidentiality and anonymity rules.

A written informed consent was provided to every participant in the study. The women were informed of the study objectives before being allocated to an arm.

The study was approved by the Research Ethics Committees of the Virgen Macarena and Virgen del Rocío hospitals (Seville, Spain) on February 24th, 2020 (Code 1936-N^− 19^).

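### Unblinded centre midwives recruit after centres are randomised, and no section fixes consent before the arm is known, so the arms can differ by who joins

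*Protocol article*

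**What the plan says.** All references are to the protocol article.

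- **Unit of allocation.** Randomization and data management: "Centres are randomized to either an intervention arm or normal care". The Analysis section confirms that health centres are the randomisation units. The experts assign centre identifiers "making a difference between the control group and the experimental group centres", so that two women at one centre do not end up in different arms.
- **A second allocation.** The same section continues: "After this randomization, women are allocated either to the intervention group or to the control group by simple random sampling", at 35 to 37 weeks. The Abstract also mentions simple randomisation of women.
- **Who recruits.** Participants, recruitment, and study area: "Midwives will explore the women’s intentions regarding breastfeeding", check the criteria, explain the study and invite women to join voluntarily. Randomization and data management says of recruitment: "This will be carried out by those midwives responsible for each health centre". There is no blinding (Study design), and the midwife leads the support groups (Intervention group).
- **Second eligibility check.** Eligibility is reviewed at the first postpartum visit, and inclusion requires that the woman is breastfeeding at 10 days (Inclusion criteria).
- **Consent.** The Data collection section reads "Once the woman is randomized to the control or intervention group and has signed the written consent" and adds that the aims had been explained to her beforehand. Ethics and dissemination: "The women were informed of the study objectives before being allocated to an arm". The latter section says that written consent was obtained, but not whether this came before or after allocation.
- **Analysis.** Effectiveness is tested by comparing exclusive breastfeeding at 6 months with Fisher's exact test. A logistic model is added only if factors turn out unequal between the groups.

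**The concern.** In a cluster trial, randomisation balances centres. It does not balance the women who enrol if they are identified and invited by someone who already knows the centre's arm. Here that person judges intention to breastfeed, makes the invitation and later re-checks eligibility against a criterion close to the primary outcome.

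The two offers also differ. One is monthly groups plus social-network support; the other is usual care with on-demand midwife appointments. Women may accept these at different rates and for different reasons, and motivation to breastfeed is an obvious candidate.

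Any resulting difference in prognosis would be read as an effect of the groups, or would hide one. Intention-to-treat among enrolled women does not repair it, because the selection happens at enrolment.

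**Working it through.** **1. The order of events**

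| Section | What it fixes | What it leaves open |
|---|---|---|
| Randomization and data management; Analysis | Centres are allocated before women are recruited | Whether a further woman-level randomisation takes place |
| Abstract; Randomization and data management | Women are also allocated by simple randomisation | How this fits with one arm per centre |
| Data collection | Information comes first; then randomisation and signed consent are named, in that order | Whether word order means time order |
| Ethics and dissemination | Information comes before allocation | When consent is given |

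There are two readings:
- *The centre sets the arm.* The arm is then fixed before any woman is approached, and the Ethics statement that women are informed before allocation cannot hold.
- *Women are randomised individually.* The Ethics statement can then hold, but the centre no longer sets the arm and the stated aim of separating centres fails.

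The first reading fits the cluster design. On either reading, no section puts consent before the woman or the recruiter knows the arm.

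**2. The plan's own sample size**

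Inputs from Study sample size: 25% against 37% (25 + 12), two-sided 5%, power 80%, loss 10%.

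- Unpooled formula: n = (1.960 + 0.842)² × (0.25×0.75 + 0.37×0.63) / 0.12² = 229.3, rounded up to 230 per arm. Then 230/0.9 = 255.6, rounded up to 256 per arm and 512 in total, as stated.
- Pooled formula: 232 per arm. Then 232/0.9 gives 258 per arm, or 516 in total.

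The stated figure reproduces and is not at issue. I use 230 per arm, since 256 × 0.9 = 230.4.

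**3. Illustration of a recruitment shift**

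Assume no true effect. The control rate is 25%, and the intervention rate is 25% + b only because of who joins. Clustering is ignored. The documents give no value for b; 3 and 5 points are assumptions.

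Normal approximation: P(reject) = Φ((b − 1.96·SE0)/SE1) + Φ((−b − 1.96·SE0)/SE1). SE0 is the pooled and SE1 the unpooled standard error of the difference.

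- b = 0.03: SE0 = √(2×0.265×0.735/230) = 0.0412, SE1 = 0.0411. Φ(−1.23) + Φ(−2.69) = 0.113.
- b = 0.05: SE0 = √(2×0.275×0.725/230) = 0.0416, SE1 = 0.0416. Φ(−0.76) + Φ(−3.17) = 0.224.

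Exact values, summing the two binomial distributions over all outcomes that reject at 5%:

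| Assumed shift | Chi-square | Fisher (planned test) |
|---|---|---|
| 0 | 5.0% | 3.9% |
| 3 points (25% v 28%) | 11.3% | 9.4% |
| 5 points (25% v 30%) | 22.5% | 19.6% |

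Fisher's test starts below 5% because it is conservative. Its relative inflation is 9.4/3.9 = 2.4-fold and 19.6/3.9 = 5.0-fold. Against the planned 12 points, these shifts are 3/12 = 25% and 5/12 = 42% of the target effect. A 3-point shift the other way would shrink a true 12-point difference to 12 − 3 = 9 points.

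**The case against.** **Stronger readings that the text does not support**

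- A reader might infer that Data collection and Ethics and dissemination contradict each other on consent. They do not. Both put information before allocation, and Ethics and dissemination does not time consent. That consent follows allocation rests on word order in a single sentence.
- A reader might infer that the Ethics statement is simply impossible. It fails only if the centre alone sets the arm, and the article also describes woman-level randomisation.
- A reader might infer that the control arm is offered nothing but questionnaires, or that bias towards the intervention is established. Control women receive usual care and on-demand appointments. No acceptance figures are given. Women who join without a group on offer could be the more motivated ones.

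**Other points on the plan's side**

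Both arms are restricted to women who intend to breastfeed, attended antenatal lessons and are breastfeeding at 10 days. This narrows the spread of motivation. CONSORT reporting is promised and the flow diagram is not visible, so the absence of a screening log cannot be inferred. Schooling and previous breastfeeding are already collected. A full analysis plan is promised and could prespecify covariates.

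**What stands**

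These points limit the size and certainty of the problem but do not remove it. Unblinded recruitment after centre allocation is stated, as are Fisher's test and conditional adjustment. An analysis plan cannot undo selection at enrolment, and it cannot adjust for feeding intention unless that is recorded before the arm is known. Table 1 lists no such measure.

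**Conclusion.** The concern holds as a design risk. Centres are allocated first, midwives who know the arm then select and invite, and no section protects consent from knowledge of the arm. The analysis described does not guard against the resulting difference in who joins. Separately, the sections on centre-level and woman-level allocation and on the timing of information must be reconciled.

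The size is unknown. Shifts of 3 or 5 points would raise the planned test's false-positive rate from 3.9% to 9.4% or 19.6%. This rests on assumed shifts, no true effect, 230 women per arm and no clustering. The direction could be either way, and no imbalance has been shown.

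**What to change.** 1. Reconcile the Abstract, Randomization and data management, Data collection, Analysis and Ethics and dissemination sections. State one unit of allocation and one sequence of information, consent and arm disclosure.
2. Invite all women at the 35 to 37 week visit consecutively, with one information sheet common to both arms.
3. Take consent and record feeding intention, parity, previous breastfeeding and schooling before the woman is told which programme her centre runs. Table 1's baseline includes birth data and so comes too late for this.
4. Log the women invited, eligible, declined and consented, by centre.
5. Make the primary analysis a prespecified model that always adjusts for these pre-birth factors and accounts for clustering by centre through a random effect or GEE. Centre fixed effects will not do, because with one arm per centre they are collinear with arm.

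**Cost.** The consent wording needs an ethics amendment, and the visit needs reordering and a short log. No extra staff are required. Some women will already know what their centre offers, and the midwife remains unblinded. The bias is therefore reduced and made visible, not removed.

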### Outcome measurements

#### Primary outcomes measurement

Type of infant feeding after the first ten days, 2, 4, and 6 months of life, depending on whether they are in the control or in the intervention group.
Exclusive breastfeeding: it means that the newborn is fed only with breast milk, without using any other milk or food, from its birth up until the first 6 months of its corrected age, carrying out the measuring at those intervals corresponding to 2, 4, and 6 months. Breastfeeding duration is defined as the period that goes from birth until the last administration of breast milk [8].Nearly exclusive breastfeeding: occasional administration of formula milk [8].Partial breastfeeding: combination of breast and formula milk [8].Formula feeding: exclusively formula milk [8].

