
Table 1 shows the measurement tools used for data collection, the method of collection and time points.

**Table 1 Tab1:** Measurement domains, survey tools, and collection time point

Variable	Component	Measurement tools/ Questions	Baseline	2mth	4mth	6mth
*Sociodemographic measures*		Age, schooling level, marital status, employment, ethnicity.	✓			
*Clinical information*	Obstetric outcomes	Type of birth, onset of labour, type of analgesia, perineal trauma, skin-to-skin technique	✓			
	Neonatal outcomes	Gender, weight, Apgar, neonatology admission, health problem	✓			
*Breastfeeding measures*	Previous experience	In affirmative case, interruption motivation	✓			
	Type of breastfeeding	Exclusive breastfeeding, nearly exclusive breastfeeding, partial breastfeeding, formula	✓	✓	✓	✓
	Breastfeeding information	Breastfeeding observation form (BREAST)	✓			
	Breastfeeding Self-Efficacy	Breastfeeding Self-Efficacy Scale-Short Form (BSES-SF)	✓	✓	✓	✓
	Breastfeeding problems	Type of problem and resolution (midwife, peer, social network, Internet …)	✓	✓	✓	✓
	Breastfeeding Interruption - Motivation			✓	✓	✓
*Behaviour measures*	Self-Efficacy General Scale		✓	✓	✓	✓
*Social networks (intervention group)*	Use and frequency			✓	✓	✓
	Problem consulted			✓	✓	✓
*Clinical services*	Appointments related to breastfeeding attended			✓	✓	✓

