### Study sample size

Taking into account that the EB rate in Andalusia is 25%, this is considered the expected value in the control group. An estimated increase effect of 12% of the EB rates at 6 months is established, as asserted in previous studies [34]. To reach this difference between both groups, a two-tail hypothesis is set out, with a power of 80% and assuming a type I error of 5%, assuming a loss of 10% in the follow-up, the necessary sample increases to 512 women, 256 in each group. Missing values in the follow-up will be addressed by multiple imputation technique, performing attrition analysis.

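### The feeding categories leave out breast milk plus other foods without formula, and exclusive breastfeeding is defined since birth but collected as current status, so the 6-month endpoint can be misclassified

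*Protocol article*

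**What the plan says.** Under Primary outcomes measurement, EB means breast milk only, "without using any other milk or food", from birth up to 6 months of corrected age. The remaining types refer only to formula: nearly exclusive is occasional formula; the third is "Partial breastfeeding: combination of breast and formula milk"; formula feeding is formula and nothing else. Table 1 lists the same set at baseline and at 2, 4 and 6 months, with no further option: "Exclusive breastfeeding, nearly exclusive breastfeeding, partial breastfeeding, formula".

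The Intervention group and Control group sections both say that follow-up collects how the infant is currently being fed. For controls, "the follow-up will be performed after the first two, four, and six months after birth"; the corresponding sentence for the intervention group says *at* those months. Under Data collection, participants supply the information themselves through the study App or an online questionnaire. Under Analysis, effectiveness is the number of women breastfeeding exclusively at 6 months in each group, compared with Fisher's exact test.

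**The concern.** The primary comparison needs a yes or no on EB at 6 months. Two features of the plan make that answer uncertain.

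- **A missing category.** A mother giving breast milk and cereal or juice but no formula fails the EB definition and meets none of the other three. Because the alternatives all mention formula, she may reasonably choose EB, and nothing else listed in Table 1 would reveal the error.
- **Two reference periods.** The Background places the end of the recommended EB period at 6 months, so other foods may be starting just when the deciding contact is made. A mother who completed 6 months of EB and then introduced foods is EB by the definition but not by current status.

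The two errors work in opposite directions on the EB rate: early solids can count as success and completed EB as failure. Equal error rates in both arms shrink the difference; unequal rates can move it either way. The trial is unblinded and only the intervention arm has monthly educational sessions, so unequal reporting is possible, though nothing in the article shows it.

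**Working it through.** **1. Are the categories exhaustive?**

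| Feeding pattern | Exclusive | Nearly exclusive | Partial | Formula |
|---|---|---|---|---|
| Breast milk only | yes | no | no | no |
| Breast milk + other food or liquid, no formula | no (other food barred) | no (needs formula) | no (needs formula) | no |
| Formula + other food, no breast milk | no | no | no | no (formula only) |

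The second and third patterns have no place.

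**2. Which period does EB refer to?** Primary outcomes measurement: since birth, to 6 months of corrected age. Follow-up text: current feeding, timed from birth. The sections agree for a mother who is still feeding only breast milk at the contact and always has. They disagree for one who completed the period and then started foods, and for one who gave other food earlier and stopped.

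**3. When is it asked?** *After* six months: Control group, and the opening line of Primary outcomes measurement. *At* six months: Abstract, Intervention group, the EB definition itself, and Analysis. No window is stated.

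**4. The plan's sample size.** The inputs given under Study sample size are these: "Taking into account that the EB rate in Andalusia is 25%, this is considered the expected value in the control group"; a 12% rise with the intervention; 80% power, two-sided 5% error; and 10% lost to follow-up. Read as 25% v 37%, with unpooled variance:

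n = (1.960 + 0.842)² × (0.25×0.75 + 0.37×0.63) / 0.12² = 229.3, so 230 per arm; 230/0.9 = 255.6, so 256 per arm and 512 in total. The stated figure is reproduced and is not in dispute. Power with 230 evaluable per arm is 79.7% (pooled normal approximation, no clustering, as in the plan's own calculation).

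**5. How many infants might lack a category?** The Discussion gives, for Spain, 46.9% any breastfeeding at 6 months and EB of just over 28.5%.

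46.9 − 28.5 = 18.4% breastfed but not exclusively. The share of these receiving no formula is not given. Assuming 25%, 50% or 75%: 4.6%, 9.2% or 13.8% of all infants.

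**6. What could that do to the comparison?** Assumed scenarios, with the same pool in both arms added to true rates of 25% and 37%:

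| Share of pool ticking EB (control / intervention) | Pool 4.6% | Pool 13.8% |
|---|---|---|
| 0.50 / 0.25 | 27.3 v 38.15: 10.85 points | 31.9 v 40.45: 8.55 points |
| 0.25 / 0.50 | 26.15 v 39.3: 13.15 points | 28.45 v 43.9: 15.45 points |
| 0.50 / 0.50 | 27.3 v 39.3: 12 points | 31.9 v 43.9: 12 points |

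In the first row, power at 230 per arm is about 70% and 48%. In the third row the difference is unchanged, but both rates are overstated by 2.3 or 6.9 points.

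**7. Equal error rates in both arms.** Observed rate p′ = p(1 − g) + f(1 − p), where f is the share of non-EB infants recorded as EB and g the share of true EB infants recorded as not EB; both are assumed.

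| f | g | Observed rates | Difference (points) | Power |
|---|---|---|---|---|
| 0 | 0 | 25.0% v 37.0% | 12.0 | 79.7% |
| 5% | 0 | 28.8% v 40.2% | 11.4 | 73% |
| 20% | 0 | 40.0% v 49.6% | 9.6 | 54% |
| 0 | 5% | 23.8% v 35.2% | 11.4 | 77% |
| 0 | 20% | 20.0% v 29.6% | 9.6 | 67% |
| 10% | 10% | 30.0% v 39.6% | 9.6 | 58% |

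With no misclassification nothing changes.

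**The case against.** The endpoint is binary, and the EB definition bars any other food. If the team knows that an infant had solids before 6 months, that infant is plainly not EB and can be coded correctly; what is certainly damaged is only the four-level description. That stands as far as it goes, but it needs information that a four-option item answered by the mother does not capture.

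A reader might infer that 6-month EB *is* misclassified. The article does not show that: the questionnaire items and coding rules are not given, so this is a risk and not a result. Nor does it follow that a mother who completed EB and then started foods has no valid answer. Under the since-birth definition she is EB; the difficulty arises only because follow-up collects current status. It would also be too strong to say that feeding is always asked once 6 months have passed, since several sections say *at*, and *after* may be loose wording in a condensed article.

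A blank answer does not go straight to multiple imputation either. Data collection says that incorrect or missing entries are checked and participants asked to complete them. That helps with blanks, but not with a plausible wrong tick.

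Finally, the illustrative figures have weak footing. The formula-free share and tick rates are assumed, the same pool is applied to two arms with different EB rates, and the 18.4% comes from 2012 national figures and not from the population behind the 25% control rate. All of this is accepted.

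**Conclusion.** The point holds as a fault in how the primary outcome is defined and collected. The categories are not exhaustive, EB is defined over one period and collected over another, and the timing wording differs between arms. As written, the plan allows both false EB (early solids without formula) and missed EB (foods begun after completing 6 months) at the deciding time point.

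Size and direction cannot be derived from the documents. Under the assumed 25% to 75% formula-free share, 4.6% to 13.8% of infants have no category, against a 12-point target. The scenarios run from no change in the difference, through dilution to 8.55 points, to inflation to 15.45 points. They show that the gap is large enough to matter, and should not be read as estimates of bias. The planned 512 women is not affected as arithmetic.

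**What to change.** In Primary outcomes measurement, Table 1 and the electronic questionnaire:

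1. Add a category for breast milk plus other foods or liquids without formula, or define partial breastfeeding as breast milk plus any other milk or food. Count either as not exclusive.
2. Define formula feeding as no breast milk, with or without other foods.
3. Use the same assessment timing wording in both arms, and state whether the 6-month date is by corrected age or from birth.
4. Ask the infant's age at first formula and at first other food or liquid. Classify 6-month EB by whether either was given before the 6-month date, whatever day the questionnaire is answered.

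The cost is one extra response option and two short questions. The observed EB rate may be slightly lower. The article says that recruitment has yet to begin, so the change is cheap now; feeding history not asked at the time is hard to recover later.
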